### Intervention

#### Group-based SE® Intervention.

Participants in the intervention arm will attend 10 weekly group sessions (3 hours/session) of manualized, group-based SE® intervention based on SE® principles. The intervention emphasizes bottom-up processing of trauma, stabilization of the autonomic nervous system, and completion of incomplete defensive responses. A Module Structure of Group-based SE® sessions is presented in Table 1.

**Table 1 pone.0336956.t001:** Module Structure of Group-based SE® sessions.

No	Module Title	Content/Activities	Intention	Target Issues	Skill Taught	Homework	Supplies
1	Preparatory 1	• Welcome and Introduction • Facilitator greeting, acknowledging courage to attend • Icebreaker: each participant states their name and one personal resource • Building cohesion and safety • Orientation exercise • Group agreement: • Psycho- education: Introduce SE**®** and PTSD • Brief explanation of trauma as incomplete defensive responses • Importance of body-based approaches and group support. • How SE**®** group can help • Experiential Exercise: • Guided practice • Invite sharing • Normalize varied responses • Integration and Group Agenda • Reflection • Collect and record group goals • Emphasize collaborative ownership process • Closing •Summarize today’s agenda • Introduce homework • Closing ritual: each participant shares one word/gesture for how they leave the session	• Build group cohesion and establish a sense of safety. • Orient participants to group purpose, structure and rules. • Introduce SE® and its relevance to PTSD recovery • Facilitate gentle re-connection to bodily sensation and resources	• Relational safety and trust. • Disconnection from the body and avoidance of interoception • Uncertainty about group role, expectations, and confidentiality • Normalization and universality (reducing isolation).	• Grounding and orienting in the present moment. • Identifying and using internal and external resources. • Sensation tracking (pleasant, neutral, unpleasant). • Respectful communication and group process skills.		• Name cards • Sensation name cards • SE®PowerPoint

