10	Returning to equilibrium & Appreciation Post Test	•Opening & Orientation •Settling into Body: Guide participant to sense their breath, contact with support surfaces and invite noticing any signs of equilibrium (ease, calm, balance). •Reflection (Identifying learning): invite participants to reflect on what they have learned over the past weeks. •Orientation: Moving from internal to External: •Reinforce appreciation for self and others. •Conduct post-group evaluation (post-test) to measure perceived changes and outcomes. •Closing ritual: group grounding (orient to space), closing circle (each participant shares one word or gesture representing gratitude or equilibrium), facilitator expresses appreciation, normalizes post group emotions, and offers resources for continued support.	•Facilitate transition from internal, trauma-focused work to external, relational engagement. •Encourage reflection on personal growth and learning from the group process. •Reinforce appreciation for self and others. •Conduct post-group evaluation (post-test) to measure perceived changes and outcomes. •Provide structured and emotionally safe closure.	•Survivors may experience anxiety about ending the group or re-entering daily social contexts. •Integration is essential: connecting inner regulation skills to real-world interactions. •Mixed feelings about closure (loss, gratitude, fear of ending) can be acknowledged and regulated. Yalom’s therapeutic factors—cohesion, universality, and existential meaning—guide the group through healthy closure.	•Orienting: shifting from internal bodily focus to awareness of others and environment. •Settling: returning to baseline and recognizing signs of equilibrium. •Social engagement: applying regulation skills while connecting externally. •Appreciation and reflection: integrating insights and achievements. •Self-regulation for transition beyond group setting.	• Continued self-care: practice daily orienting and resourcing in daily environments. • Reflection journal: write about ongoing sensations of safety, vitality, or connection. • Connection exercise: identify one supportive person or activity to maintain engagement post-group. • Optional: create a *personal grounding plan* for times of stress or overwhelm.	SE® PowerPoint

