### Treatment As Usual (TAU)

Participants in the control arm will receive five group counselling sessions (90minutes per session) over five weeks. These sessions focus on psychoeducational counseling session, covering basic mental health support strategies and coping techniques, and are facilitated by licensed psychologist. The decision to provide five 90 minute per sessions is based on evidence from Indonesian research and practice, which showing that survivors of sexual assault typically receive between 4–7 session of psychological support(Ayudia et al. 2025c; Sumekar and Sunawan 2019).

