#### Outcome Measures and Timing.

Outcomes will be measured at four time points:

**T0**: Baseline (Week 0)**T1**: Post-treatment (Week 10)**T2**: 1-month follow-up (Week 14)**T3**: 3-month follow-up (Week 22)

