### Data collection and management

#### Data collection personnel.

Data collection will be carried out by trained research assistants who are postgraduate psychology students with prior experience in research. These assistants will receive additional training on ethical handling sensitive data, trauma-informed interviewing, and scoring procedures for standardized instruments. Data collectors will be blinded to group allocation to minimize bias.

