#### Participant retention and follow-up.

To promote participant retention and ensure complete follow-up, weekly contact and reminder messages will be provided through phone and WhatsApp by research assistants. For participants who discontinue or deviate from intervention protocols, outcome data from all completed assessments will be retained for intention-to-treat (ITT) analysis.

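### A post-test is written into the last SE group session at about Week 10; if it is T1, the primary outcome is taken in a different setting by arm, and collector blinding is not protected as written

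*Protocol article*

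**What the plan says.** **Setting.** In the protocol article, Table 1 titles the tenth SE session "Returning to equilibrium & Appreciation Post Test". Both its activities and its intentions include "Conduct post-group evaluation (post-test) to measure perceived changes and outcomes". In the activities column this item comes after the settling, reflection and appreciation items and before the closing ritual.

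**Timing.** Under Group-based SE® Intervention: "Participants in the intervention arm will attend 10 weekly group sessions (3 hours/session". Under Treatment As Usual (TAU): "Participants in the control arm will receive five group counselling sessions (90minutes per session) over five weeks". Under Outcome Measures and Timing, T1 is "Post-treatment (Week 10"; T2 is Week 14 and T3 is Week 22.

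**Administration.** Platform and tools used has the outcome measures given as REDCap forms, with paper as an alternative, in the same terms for both arms. It does not say where the forms are completed or who is present.

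**Blinding.** Data collection personnel gives the task to research assistants and states "Data collectors will be blinded to group allocation to minimize bias". The next section, Participant retention and follow-up, says that "weekly contact and reminder messages will be provided through phone and WhatsApp by research assistants". Randomization and Blinding says that allocation is not concealed from the study coordinator or the group facilitators, and that participants cannot be blinded.

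**The concern.** The primary outcome is a symptom checklist completed by women who know their arm. The protocol accepts this, and it cannot be avoided. A difference between arms in where, when and in whose company the checklist is completed can be avoided.

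If T1 is taken inside session 10, the SE arm answers straight after exercises that direct attention to calm and appreciation, in the presence of the facilitators. The control arm answers in some other setting. Demand effects of this kind would probably lower SE scores, so the bias would favour SE. Women who have stopped attending would not be in the room, so missingness at T1 could depend on attendance in one arm only, and the imputation assumes missing at random.

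The second issue concerns staffing. Weekly contact over a ten-week or a five-week course can reveal the arm to whoever makes it. If outcome collectors make it, their blinding is not secure.

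**Working it through.** **1. Is the session-10 post-test T1?**

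| Evidence | Where | Points to |
|---|---|---|
| Title contains a post-test | Table 1, session 10 | T1 |
| Ten weekly sessions, so session 10 is at about Week 10 | Group-based SE® Intervention | T1 |
| T1 is post-treatment at Week 10 | Outcome Measures and Timing | T1 |
| Session feedback is already covered by SRS and HAT | Intervention fidelity and monitoring | T1 |
| Instruments listed are PCL-5, CD-RISC-25, WHOQOL-BREF, SRS and HAT; no separate group-evaluation form | Platform and tools used | T1 |
| The item refers to perceived change and names no instrument | Table 1, session 10 | Open |
| Supplies list only the presentation | Table 1, session 10 | Open |

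Reading it as T1 is a strong inference but is not stated.

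**2. Is there a control counterpart?** Counselling runs "over five weeks", which leaves 10 − 5 = 5 weeks between its end and T1. No in-session test is described for that arm.

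**3. Does the staffing protect blinding?** One role, research assistant, holds both tasks. The documents neither say that the same individuals do both nor that they are kept apart. Recruitment and setting also describes messages sent the day before each session with its agenda, but names no sender.

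**4. Scale, for illustration only.** The plan's sample size reproduces. For 2:1 allocation, d = 0.5, two-sided α = 0.05 (sidedness assumed) and power 0.80:

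- Control n = (1 + 1/2)(1.960 + 0.842)² / 0.5² = 47.1, so 48; SE n = 2 × 48 = 96.
- With 30% attrition: 48/0.70 = 68.6, so 69; 96/0.70 = 137.1, so 138. The total is 207, as stated.

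Expected completers are 0.70 × 138 = 96.6 and 0.70 × 69 = 48.3, about 97 and 48. The standard error of d is about √(1/97 + 1/48) = 0.1765.

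Suppose there is no true effect and the T1 setting alone shifts the difference by b SD in favour of SE (b is assumed; the documents give no figure). The two-sided rejection rate is Φ(b/0.1765 − 1.96) + Φ(−b/0.1765 − 1.96).

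| b (SD) | Share of d = 0.5 | Rejection rate, 97/48 | Noncentral t, 96/48 |
|---|---|---|---|
| 0 | 0% | 5.0% | 5.0% |
| 0.1 | 20% | 8.7% | 8.7% |
| 0.2 | 40% | 20.5% | 20.3% |

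**5. What this does not measure.** These rates belong to one two-group comparison at T1. The Statistical analysis plan section specifies a mixed model over T0 to T3 with a Bonferroni correction across outcomes. T2 and T3 are not placed in a session. In a contrast averaging T1, T2 and T3 equally, for example, a shift at T1 alone would enter as b/3, or 0.03 to 0.07 SD for the range above.

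**The case against.** The strongest reply is that the article never says the PCL-5 is given in session 10. The post-test could be a separate group evaluation. Data collection is assigned to research assistants rather than to facilitators, and REDCap forms can be completed anywhere. This stands in part: it is why the finding is conditional. A reader might infer that the primary outcome is definitely measured differently by arm, but the documents do not state this. What remains is that, followed as written, session 10 contains a post-test of outcomes in the week of T1, and nothing separates the two.

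A reader might also infer that the stated blinding fails. The text does not support that. The overlap is of role, separate assistants could do each task, and the retention section speaks of weekly contact rather than session reminders. The supportable wording is that blinding is not protected as written. Because the PCL-5 is self-report, collector blinding also gives only limited protection, so the setting is the weightier part.

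Attendance-dependent missingness is likewise possible but not shown. Nothing restricts T1 to those in the room, and the retention section aims for complete follow-up and keeps the completed assessments of those who discontinue.

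Finally, an article may leave assessment logistics to the full protocol. That would excuse silence. It does not excuse a session plan and a T1 schedule that coincide in one arm only, or two adjacent sections that give one role a blinded task and a task that can unblind.

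**Conclusion.** The point holds in conditional form. If the session-10 post-test is T1, the primary outcome at the only end-of-treatment assessment is collected in the therapy setting in the SE arm and elsewhere in the control arm, with a risk of bias in favour of SE. T2 and T3 are not exposed in this way, so the planned mixed model is affected mainly through T1.

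The size is unknown. The 9–20% range rests on an assumed shift of 0.1 to 0.2 SD, about 97 and 48 completers, no true effect and a simple T1 comparison. It should not be read as the trial's Type I error rate under its planned analysis. No change in sample size follows.

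The staffing point is secondary: the blinding statement and the reminder statement need to be reconciled.

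**What to change.** 1. Take the T1 outcome measures out of session 10, or state in Table 1 that the session-10 post-test is not T1 and name what it is.
2. Collect T1 in both arms by the same individual REDCap or paper procedure, outside any session, in one common window (for example Week 10 to 11), whether or not the participant is still attending.
3. Give weekly reminders and session messages to the study coordinator, who is already unblinded, or to assistants who do not collect outcomes. Say so under both Data collection personnel and Participant retention and follow-up.

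The cost is an edit to Table 1 and two paragraphs, with no extra staff. The downside is small: T1 needs its own reminder, and completion at session 10 is no longer automatic. The change should be made before the first T1 assessment, because T1 cannot be collected again later.

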#### Discontinuation criteria.

Participants may discontinue participation at any time upon their own request, or if the facilitator identifies significant emotional distress requiring individual therapy. In such cases, participants will be referred for appropriate psychological support. As the intervention is non-pharmacological, no modification of dosage or session content will be applied.

### Concomitant care

Participants may continue receiving any ongoing counselling or medical care throughout the trial. However, initiation of new trauma-focused therapy during trial participation is discouraged to avoid potential confounding effects on the study outcomes.

### Ancillary and post-trial care

Participants who experience psychological distress related to the intervention or trial participation will be offered post-trial psychological support and referral to university counselling services. No financial compensation is provided, but free psychological follow-up will be available on request.

### Intervention fidelity and monitoring

Each group-based SE® session will be delivered by trained SE® practitioners and supervised by a senior clinical psychologist. At the end of each session, participants will complete:

**Session Rating Scale (SRS)** for therapeutic alliance**Helpful Aspects of Therapy (HAT)** form for qualitative feedback

Grounding exercises will be conducted before and after each session to promote emotional regulation.

### Treatment As Usual (TAU)

Participants in the control arm will receive five group counselling sessions (90minutes per session) over five weeks. These sessions focus on psychoeducational counseling session, covering basic mental health support strategies and coping techniques, and are facilitated by licensed psychologist. The decision to provide five 90 minute per sessions is based on evidence from Indonesian research and practice, which showing that survivors of sexual assault typically receive between 4–7 session of psychological support(Ayudia et al. 2025c; Sumekar and Sunawan 2019).

#### Outcome Measures and Timing.

Outcomes will be measured at four time points:

**T0**: Baseline (Week 0)**T1**: Post-treatment (Week 10)**T2**: 1-month follow-up (Week 14)**T3**: 3-month follow-up (Week 22)

#### Primary outcomes include:

PTSD Checklist for DSM-5 (PCL-5): Primary outcome measure assessing PTSD symptoms. Indonesian version Cronbach’s α = 0.93

**Secondary outcomes include:**

Connor-Davidson Resilience Scale (CD-RISC-25)WHO Quality of Life-BREF (WHOQOL-BREF): Assesses physical, psychological, social, and environmental quality of life. Cronbach’s α range: 0.41–0.77

**Other measures include:**

Sociodemographic questionnaire: Collects age, marital status, occupation, education, and medical history.Structured Clinical Interview for DSM-5 (SCID-5): Used for diagnostic confirmation of PTSD and exclusion criteria

### Sample size

A priori power analysis using G*Power 3.1 estimated a required total sample size of 207 participants (138 intervention, 69 control) to detect a medium effect size (Cohen’s d = 0.5), with α = 0.05, power = 0.80, and accounting for 30% attrition.

The choice of medium effect size (d = 0.5) is based on prior meta-analytical findings from studies evaluating SE® and other body-oriented trauma interventions among individual PTSD or complex trauma symptoms. Specifically, Payne et al [7] and Andersen et al [16–18] report medium to large effect sizes in PTSD symptom reduction following SE® informed interventions. Given the cultural adaptation and group-based format in this study, a conservative medium effect size was deemed appropriate.

Participants will be randomized in a 2:1 allocation ratio using block randomization generated through Castor EDC software.

### Data collection and management

#### Data collection personnel.

Data collection will be carried out by trained research assistants who are postgraduate psychology students with prior experience in research. These assistants will receive additional training on ethical handling sensitive data, trauma-informed interviewing, and scoring procedures for standardized instruments. Data collectors will be blinded to group allocation to minimize bias.

#### Participant retention and follow-up.

To promote participant retention and ensure complete follow-up, weekly contact and reminder messages will be provided through phone and WhatsApp by research assistants. For participants who discontinue or deviate from intervention protocols, outcome data from all completed assessments will be retained for intention-to-treat (ITT) analysis.

#### Platform and tools used.

All outcome measures, including PCL-5, CD-RISC-25, WHOQOL-BREF, SRS, HAT will be administered using secure digital forms hosted on REDCap (Research Electronic Data Capture), a HIPAA-compliant, encrypted online platform. In cases where participants have limited internet access or prefer paper-based administrations, hard-copy versions will be made available and later digitized into the REDCap system by data entry personnel.

#### Confidentiality.

All participant data will be de-identified prior to analysis. Electronic data will be stored on a secure, encrypted university server accessible only to authorized research personnel. Hard-copy documents will be stored in locked cabinets within the Department of Clinical Psychology. Data will be retained for five years after publication, after which it will be permanently deleted. Only the principal investigator and data analyst will have full access to the de-identified dataset

### Statistical analysis plan

All statistical analyses will be performed using SPSS version 22.0.

Descriptive statistics will be used to summarize demographic and clinical characteristics of the participants.Baseline differences between groups will be examined using chi-square test for categorical variables and t-test for continuous variables.To evaluate treatment effects, linear mixed-effect models will be used to analyse the interaction of time (T0, T1, T2, T3) and group condition (intervention vs control) on primary and secondary outcomes.The models will include fixed effects for time, group, and time x group interaction, and random intercepts for participants to account for within subject variability across time points.To minimize confounding related to unequal treatment exposure, total professional contact time (minutes) within and outside the study will be logged for each participant. In prespecified secondary analyses, this variable will be included as a covariate in the mixed-effects models. Additional sensitivity analyses will be conducted, including (i) exclusion of participants who receive substantial trauma-focused services outside the protocol, (ii) per-protocol analyses restricted to participants with adequate adherence (≥ 80% of assigned sessions), and (iii) exploratory dose-response models testing the interactions between group assignment and contact time. These steps will allow us to assess whether intervention effects remain robust after adjusting for variation in professional contact time.Effect sizes will be reported using Cohen’s d.All analyses will follow the intention-to-treat (ITT) principle, including all randomized participants. Missing data will be handled using regression imputation under the assumption that data are missing at random (MAR). Specifically, predictive mean matching will be used to impute missing continuous outcome variables, which is considered appropriate for longitudinal clinical trial data.

To control for the increased risk of Type I error due to multiple comparisons across outcomes, A Bonferroni correction will be applied.

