### Participants

#### Eligibility criteria.

Inclusion criteria:

Female, aged 18 -45 yearsA self-reported history of sexual assaultPTSD symptoms in the mild to moderate range (PCL-5 score ≥ 39)Trauma occurred ≥ 6 months prior to enrollment (to ensure symptom stability and chronicity)Not currently receiving trauma-focused psychological treatment or medication within the last 30 days

Exclusion criteria:

Substance or alcohol misuseOngoing severe mental illness (e.g., psychosis, bipolar disorder, organic brain disorders)PTSD symptoms arising in conjunction with a diagnosed medical conditionCurrent suicidal ideation requiring emergency care

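### The 207 is sized for one two-group comparison, but the planned test is a time × group interaction over T0–T3 with no named contrast or visit, so the stated 80% power belongs to no planned analysis

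*Protocol article*

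**What the plan says.** The Sample size section reports a G*Power calculation for 207 participants (138 and 69) "to detect a medium effect size (Cohen’s d = 0.5), with α = 0.05, power = 0.80, and accounting for 30% attrition". It names no test, visit, number of measurements or within-person correlation.

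The Statistical analysis plan section says that "linear mixed-effect models will be used to analyse the interaction of time (T0, T1, T2, T3) and group condition (intervention vs control"). The same model serves PCL-5 and the secondary scales. The fixed effects are time, group and their interaction, and the only random effect is a participant intercept. T0 is thus a response with its own free group difference, and no baseline covariate is listed.

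The outcome sections make PCL-5 primary and list Weeks 0, 10, 14 and 22, but single out no visit. Eligibility requires "PCL-5 score ≥ 39". A Bonferroni correction is described across outcomes, not across visits.

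**The concern.** Three features of the stated model deserve attention.

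- **The powered quantity is not the tested one.** A four-level time factor crossed with two arms gives a 3-df interaction. That test can be significant without SE being better at any particular visit, and its power depends on the shape of the effect over time and on the within-person correlation. Neither enters the sample size. With no primary visit, and a multiplicity rule that does not cover visits, a significant interaction could be read through whichever visit looks best.
- **Baseline is used inefficiently.** With T0 as a response and a free group effect at T0, each visit contrast is a difference in change from baseline. Adjusting for T0 is more precise.
- **The covariance is restrictive.** A random intercept alone imposes one variance and one correlation on all visits from Week 0 to Week 22. If correlations decay, or baseline is narrowed by the entry threshold, standard errors for single-visit contrasts may be wrong.

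**Working it through.** **1. Reproducing 207.** Inputs from Sample size: d = 0.5, α = 0.05, power 0.80, 2:1 allocation, 30% attrition.

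- Control n = (1 + 1/2)(1.960 + 0.842)² / 0.5² = 47.1, so 48; intervention 96. The exact t calculation also gives 48 + 96.
- 48/0.7 = 68.6, so 69; 2 × 69 = 138; total 207.
- Alternatives that do not give 207: one-sided 2:1 (163), two-sided 1:1 (180 normal, 183 t), and multiplying by 1.3 instead of dividing by 0.7 (188).

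No repeated-measures quantity is needed to reach the figure.

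**2. Power of the analyses the model could deliver.** Evaluable: 207 × 0.7 ≈ 145, taken as 97 and 48, so 1/97 + 1/48 = 0.03114. The within-person correlation r is not given; 0.3 to 0.7 is assumed. SD is 1 at every visit, with compound symmetry.

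- Two-sample t at one visit: noncentrality 0.5/√0.03114 = 2.83.
- Week-10 change contrast: variance factor 2(1 − r), noncentrality 2.83/√[2(1 − r)], 143 df.
- Week-10 adjusted for T0: variance factor 1 − r², noncentrality 2.83/√(1 − r²), 142 df.
- 3-df interaction: λ = SS/[(1 − r) × 0.03114], with 3 and 429 df. SS is the sum of squared deviations of the four arm differences from their mean. It is 0.1875 for (0, 0.5, 0.5, 0.5) and 0.14 for (0, 0.5, 0.4, 0.3). At r = 0.5, λ is 12.04 and 8.99.

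| r | t test | Change | Adjusted | 3-df, sustained | 3-df, waning |
|---|---|---|---|---|---|
| 0.3 | 80% | 66% | 84% | 68% | 54% |
| 0.4 | 80% | 73% | 87% | 76% | 62% |
| 0.5 | 80% | 80% | 90% | 84% | 71% |
| 0.6 | 80% | 88% | 94% | 92% | 81% |
| 0.7 | 80% | 95% | 98% | 97% | 91% |

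The variance ratio of change to adjusted is 2(1 − r)/(1 − r²) = 2/(1 + r), which runs from 1.54 at r = 0.3 to 1.18 at r = 0.7.

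**3. If T0 is truncated at 39.** Assume an untruncated mean of 42 and SD of 16. Then a = (39 − 42)/16 = −0.1875, the normal hazard at a is h = 0.682, and the share of T0 variance left is k = 1 + a·h − h² = 0.41. In untruncated units the Week-10 variance is v = r²k + 1 − r², the change variance is v + k − 2rk, and the adjusted variance is 1 − r². At r = 0.5, v = 0.852, the change variance is 0.852 and the adjusted variance 0.75, so adjustment saves 12%. The T0–T1 correlation falls from 0.5 to 0.35. With d scaled to the Week-10 SD, change versus adjusted power is:

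- r = 0.4: 77% vs 83%
- r = 0.5: 80% vs 85%
- r = 0.6: 84% vs 88%
- r = 0.7: 89% vs 91%

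The gap is about 2 to 6 points over this range. At r = 0.3 it is 74% vs 82%.

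**4. Random intercept only (simulation, no treatment effect).** Type I error of the T3 − T0 contrast was 0.050 under compound symmetry, 0.102 under AR(1) with correlation 0.6, and 0.081 under an assumed random-slope structure. With truncated T0 and decaying correlations, the Week-10 contrast had 0.079; with truncated T0 and flat correlations, contrast error was not inflated. The 3-df test stayed between 0.049 and 0.064 throughout.

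**The case against.** A time × group mixed model with baseline among the responses is a common and valid analysis of a randomised trial. The word omnibus does not appear in the article, and a single-visit contrast can be drawn from the same model. Contrasts and covariance are also things a full analysis plan often settles. That is fair, but the article has a section called Statistical analysis plan that fixes the test, the fixed effects and the random effect, and the point rests on what is stated there. A contrast is permitted, but none is named.

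Four stronger readings are tempting, and the document does not support them.

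- **The trial is underpowered.** No correlation or time course is given. For a sustained d of 0.5, the 3-df test exceeds 80% from r of about 0.5 upward; even the waning pattern reaches 81% at 0.6.
- **Baseline is wasted.** It serves as the reference for change. The loss is one of efficiency.
- **The eligibility rule breaks the covariance assumption.** The article does not say that the screening PCL-5 is the T0 value. If T0 is measured separately, it need not be truncated at 39. If it is truncated, the large equal-variance gain from adjustment cannot also be claimed.
- **Type I error is about 8%.** That holds for single-visit contrasts under assumed decaying correlations. The interaction test itself stays near nominal.

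**Conclusion.** The mismatch stands. The 207 matches a single two-sample comparison of means, while the stated analysis is an interaction over four visits with no named contrast, so the 80% attaches to no planned test. Depending on r (0.3 to 0.7), the interaction test could have 68 to 97% power for a sustained effect and 54 to 91% for the waning one. These ranges assume 97 and 48 evaluable, equal variances and compound symmetry.

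The efficiency loss is real but uncertain in size: 2 to 18 power points under equal variances, and about 2 to 6 if T0 is truncated as assumed with r of 0.4 to 0.7. The random intercept is a restrictive choice that may misstate single-visit standard errors; whether it does depends on correlations the article does not give. This is a worthwhile and nearly free correction to a stated model. It does not show that the trial will fail or that its interaction test is invalid.

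**What to change.** Name one primary contrast before outcomes are seen, for example the SE minus TAU difference in PCL-5 at Week 10, which the article already labels post-treatment. Estimate it from a mixed model with T1 to T3 as responses, arm × visit, T0 PCL-5 (× visit) as covariate, and an unstructured residual covariance. SPSS MIXED can fit this with a REPEATED statement and COVTYPE(UN). Make Weeks 14 and 22 and the 3-df interaction secondary, and use the same model form for CD-RISC-25 and WHOQOL-BREF. In Sample size, state that the 80% refers to this contrast, conservatively computed without baseline adjustment.

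The cost is wording only: no extra participants, visits or data. Recruitment is scheduled for January to June 2026 and no interim analyses are planned, so the choice can be fixed before outcome data are examined. The small downside is that the headline rests on one visit.
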